### Discontinuation and drop-out criteria

2.6

The following are the criteria for discontinuation from the study:

(1)withdrawal of consent to participation in the study by the subject or their legal representative;(2)discovery of violation of inclusion criteria or presence of exclusion criteria during the course of research;(3)loss to follow-up;(4)judgement of unsuitability for continuation in the study based on the discretion of the investigator in charge.

### Ethics

2.7

The study protocol has been approved by the Institutional Review Board of Wonkwang University Iksan Korean Medicine Hospital (WKUIOMH-IRB-2018-05) and has been registered in the Clinical Research Information Service, Republic of Korea (KCT0003630). It accords with the Declaration of Helsinki. Written informed consent will be obtained from the participants and the legal representatives before enrolment in the study. If the subject is under 7 years old, written informed consent will only be obtained from the legal representatives.

## Discussion

3

This is a study protocol to investigate the association of AD with obesity in the Korean population and verify its mechanism by analyzing gut microbiome–metabolome–immune biomarkers using a multi-omics approach.

In this study, we included 4 to 12-year-old children as subjects for several reasons. First, AD is one of the most common chronic childhood skin diseases, affecting up to 15% to 20% of children worldwide.^[16,17]^ Given that the symptoms of AD usually begin in infancy, the majority of AD cases develop before the age of 5 years,^[18,19]^ and the prevalence in teenagers seems to be falling significantly,^[20]^ children aged 4 to 12 have a high prevalence of AD. Second, most children aged 4 to 12 years in Korea, spend most of their time in a group setting, such as a kindergarten or school, eating a similar Korean-style diet consisting of rice, soup, and side dishes. Third, it is known that the phylogenetic composition of bacterial communities evolves towards an adult-like composition within 3 years after birth.^[21]^

In the present study, a 3-day controlled diet will be provided to ensure better dietary control, and fecal samples will be collected both before and after controlled meals. It is now understood that diet plays a significant role in shaping the microbiome, with experiments showing that dietary alterations can induce large, temporary microbial shifts within 24 hours.^[22,23]^ Because there is no appropriate guideline in terms of dietary control in microbiome analysis, we assumed that 3-day-controlled meal is sufficient to eliminate effects of diet. We also will analyze microbial changes before and after the 3-day meal to confirm whether the 3-day controlled meal is sufficient to remove microbial changes due to diet.

This study protocol represents a unique opportunity to enhance our understanding of the association between AD and obesity in terms of gut microbiome, metabolome, and immunological mechanisms and may, therefore, serve to improve future management strategies for AD.

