### Study design and procedure

2.2

This case-control study will be conducted at Wonkwang University Iksan Korean Medicine Hospital in the Republic of Korea. The study has 4 arms: an obese/overweight with AD group, a normal/underweight with AD group, an obese/overweight control group, and a normal/underweight control group. Twenty subjects will be assigned to each arm and a total of 80 subjects will be recruited for this study.

After potential participants voluntarily consent to the study, they will be screened using predetermined inclusion/exclusion criteria at the first visit. To be assigned to a group, subjects will be evaluated based on demographic characteristics, medical history, and physical examination including Hanifin & Rajka AD criteria. The SCORing of AD (SCORAD) index, the Children's Dermatology Life Quality Index (CDLQI), and the Korean Gastrointestinal Symptom Rating Scale (KGSRS); body composition analysis will also be performed to confirm the subjects’ general health and disease status.

The 3-day controlled meal will be provided to the subjects in order to reduce microbial changes due to variable food intake. The 3-day meal is prepared in an allergy-free manufacturing facility and is free of eggs, milk, soy, and wheat, which are known to be the main causes of food allergies.

After the 3-day meal, SCORAD index, CDLQI, KGSRS, and body composition analysis will be evaluated. Blood and fecal samples will be obtained after the controlled meal in order to analyze microbiome-metabolome-immune biomarkers. A fecal sample will also be obtained before the controlled meal in order to assess the microbial differences between the experimental groups before and after the controlled meal. The detailed design is summarized in Figure 1.

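### A before-after change in the fecal microbiome cannot confirm that the 3-day meal was sufficient to remove diet effects; a paired comparison of between-child dispersion fits the question better, and even that shows only partial convergence

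*Protocol article*

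**What the plan says.** Section 2.2 (Study design and procedure) gives the meal's purpose: it is provided "in order to reduce microbial changes due to variable food intake". Every participant receives it ("The 3-day controlled meal will be provided to the subjects"). There is one fecal sample before the meal and one after. The pre-meal sample is taken "to assess the microbial differences between the experimental groups before and after the controlled meal".

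The Discussion (section 3) goes further. It says that there is no suitable guideline on dietary control, and then: "we assumed that 3-day-controlled meal is sufficient to eliminate effects of diet". It names the check on that assumption: "We also will analyze microbial changes before and after the 3-day meal", with the stated aim "to confirm whether the 3-day controlled meal is sufficient to remove microbial changes due to diet". Just before this, it gives as background that "dietary alterations can induce large, temporary microbial shifts within 24 hours".

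Section 2.5 (Statistical plan) lists alpha diversity measures and weighted and unweighted UniFrac distances. It ties none of them to the meal check.

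**The concern.** The meal is meant to remove a source of variation between children, namely what each child habitually eats. Success would mean that children become more alike once they eat the same food. The evidence named is a different quantity: whether the microbiome changed from before to after.

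- **Change observed.** On the article's own 24-hour premise, a new uniform meal is expected to move the microbiome. That movement can sit on top of habitual-diet differences that remain intact.
- **No change observed.** This could mean that diet had little effect, that three days were too short, or that children converged around an unchanged average.

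Neither result separates sufficient from insufficient diet control. No arm without the meal and no third sample is described that could do so. The stake is the interpretation of the post-meal microbiome comparisons. If habitual diet differs between the BMI or AD groups, a misread check would present residual diet confounding as controlled.

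**Working it through.** The article gives no figure for this check, so there is none to reproduce. The group sizes agree with the total (4 × 20 = 80). All variances and shifts below are assumptions; only n = 80 comes from the article.

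**Model.** For one microbiome feature in one child:

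- before = host + diet + noise
- after = host + w × diet + common shift + noise

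Here w is the fraction of the child's habitual-diet effect that persists (w = 1, nothing removed; w = 0, all removed).

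**Step 1: does average change track removal?** Variances: host 1, diet 1, noise 0.5. Paired t-test, two-sided 0.05, n = 80, 3,000 runs per row.

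| Truth | Average change significant | Correlation with habitual diet, before → after |
|---|---|---|
| Shift 0.5, nothing removed | 98.9% | 0.63 → 0.63 |
| No shift, all removed | 5.5% | 0.63 → 0.00 |
| Shift 0.5, all removed | 87.2% | 0.63 → 0.00 |
| No shift, nothing removed | 5.2% | 0.63 → 0.63 |

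The test follows the shift, not the removal. A hand check of row 1: the difference has variance 0.5 + 0.5 = 1, so SE = 1/√80 = 0.112 and z = 0.5/0.112 = 4.5.

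**Step 2: does between-child spread track removal?** A second set of assumptions: SDs of diet 0.7, host 0.5, noise 0.5, so variances 0.49, 0.25, 0.25. The test is Pitman-Morgan for paired variances, with r = (V_before − V_after) / √[(V_before + V_after)² − 4·cov²] and power ≈ Φ(atanh(r)·√(n − 3) − 1.96).

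- All removed: V_before = 0.99, V_after = 0.50, cov = 0.25. r = 0.49/√(1.49² − 0.25) = 0.349 and atanh(r) = 0.364.
  - n = 80: 0.364 × √77 = 3.20, power 89%. Centring within four groups of 20 costs about one point (88% by simulation).
  - n = 20: 0.364 × √17 = 1.50, power 32%. Requiring significance in all four groups would succeed in about 0.32⁴ ≈ 1% of studies, even with all diet variation removed.
- Nothing removed: 5%, with or without a common shift.
- Half the effect kept (w = 0.5): V_after = 0.25 × 0.49 + 0.50 = 0.6225, cov = 0.25 + 0.5 × 0.49 = 0.495. r = 0.3675/√(1.6125² − 0.9801) = 0.289, power 74%.

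Under the Step 1 variances the same test rejects in 74–75% (all removed), 5% (nothing removed) and 61% (w = 0.5).

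**Step 3: does reduced spread prove sufficiency?** Let s be the diet share of the pre-meal variance and w² the fraction of diet variance kept. The after/before variance ratio is (1 − s) + w²s.

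- s = 0.4, w² = 0: ratio 0.60; diet makes up 0% of the remaining variance.
- s = 0.8, w² = 0.5: ratio 0.2 + 0.4 = 0.60; diet makes up 0.4/0.6 = 67% of the remaining variance.

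The same ratio fits complete removal and a large residual. Two time points without a measure of habitual diet cannot tell them apart.

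**The case against.** The strongest reply is that the article does not say which statistic the check will use. It speaks of microbial changes, and the UniFrac distances in section 2.5 could be used to examine convergence. A condensed article may leave that choice to the full protocol or analysis plan. This stands in part: a reader might infer that a mean shift will be tested, but the document does not say so, and the simulation illustrates one natural reading. It does not rescue the stated conclusion. By Step 3, no analysis of these two samples alone confirms sufficiency, so a later choice of statistic would not make the sentence true.

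Three stronger readings are not supported.

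- **Paired samples treated as independent.** The independent-samples tests in section 2.5 are assigned to AD versus non-AD and obese versus non-obese comparisons, which involve different children. Nothing says that they will be applied to the two samples from one child.
- **Every group comparison depends on the check.** Section 2.2 already plans group comparisons on both sides of the meal, and the pre-meal one does not need the meal to work. The diet rationale concerns the microbiome; the article does not tie the serum metabolome or immune markers to it.
- **The protocol claims elimination throughout.** Section 2.2 aims only to reduce diet-related changes. The overstatement is in the Discussion.

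It is also fair that the check is supporting rationale and not a study objective.

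**Conclusion.** The point holds as a flaw of inference. The Discussion names both the evidence (before-after change) and the conclusion (sufficiency confirmed), and its own 24-hour premise breaks the link. This does not depend on the assumed variances. The percentages do: they illustrate a single feature with normal errors, and the power of a UniFrac dispersion test may differ. The consequence is moderate. The check is secondary, but the reading of the post-meal microbiome comparisons leans on it. It should be corrected, because a more relevant analysis needs no new data.

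**What to change.** 1. Make the diet-control check a paired comparison of between-child UniFrac dispersion before versus after the meal. Pool all 80 children after centring by group (at each time point, so that a common shift does not enter the measure), and permute the time labels within child. Do not rest the check on separate tests in groups of 20.
2. Report the before/after dispersion ratio with its interval. Treat a reduction as evidence of partial convergence only, and a non-significant result as inconclusive.
3. Read the result alongside the pre- and post-meal group comparisons already planned in section 2.2.
4. In the Discussion, replace the statements that sufficiency will be confirmed and that diet effects are eliminated. Say that the meal reduced between-child variation to the extent observed.

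The cost is analysis and wording; both fecal samples are already in the design. The downside is that the check may show little convergence and so weaken the diet-control claim.
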